## Trial management

This trial was registered at ClinicalTrials.gov with registration number NCT04951804 and conducted at the CHUM only. [name] RN, who has extensive experience in clinical trials, will ensure proper trial conduct and all data collection. He will ensure proper study start-up and adaptation of the consent form. He will oversee participant enrolment, the randomization process, data collection, the timely reporting of adverse events and serious adverse events to the CRCHUM Research Ethics Board (REB), and data collection. He will ensure adherence to standard operating procedures of the CRCHUM.

## Data safety monitoring board (DSMB)

A selected group of clinicians and clinical researchers will oversee this study’s DSMB. This will include an EUS-MD from outside CHUM. Members of the DSMB will not be involved in the conduct of the trial and their participation will be void of any professional or financial bias that may hinder their independent decision making. This committee will meet before trial initiation and meet every three months to review possible AEs. Each reviewer will be blinded to the group allocation. At the first meeting, the DSMB will discuss the protocol and decide on criteria to review the data as well as monitoring of the study. The following meetings will be divided into an open and close sessions. During the open session, the PI, statistician, and all members of the DSMB will be present. The PI will present to the committee the participants’ demographic characteristics, protocol compliance, quality control, timeliness and completeness of follow-up, and all adverse events. During the closed session, the DSMB alone will review the safety data. At the end of each meeting, the members of the DSMB will vote to continue, modify, or terminate the study. The DSMB will provide a written report to the REB and PIs about their conclusion.

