**Discussion:**

We hypothesize that bupivacaine is superfluous and may actually reduce pain control by diluting the neurolytic effect of alcohol. Bupivacaine is also potentially dangerous in that it may produce serious adverse events such as arrythmias and cardiac arrest if inadvertently injected intravascularly.

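### The DSMB is blinded to allocation with no exception and no stated way to unmask, so it could not attribute an excess of harm to the bupivacaine arm

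*Protocol article*

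**What the plan says.** The section on the data safety monitoring board in the protocol article fixes five things that matter here.

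- Frequency and purpose: the board is to "meet every three months to review possible AEs".
- Masking: "Each reviewer will be blinded to the group allocation". No exception is given for the closed session or for a safety signal, and no way to request the allocation is described.
- Sessions: "During the open session, the PI, statistician, and all members of the DSMB will be present", and there the principal investigator presents, among other items, all adverse events. Then, "During the closed session, the DSMB alone will review the safety data". The text does not say whether those data are pooled or split by arm.
- Decision: "At the end of each meeting, the members of the DSMB will vote to continue, modify, or terminate the study".
- Working rules: at its first meeting the board will "decide on criteria to review the data as well as monitoring of the study".

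Elsewhere the article names a hazard of one arm. The Discussion part of the abstract says: "Bupivacaine is also potentially dangerous in that it may produce serious adverse events such as arrythmias and cardiac arrest", in connection with accidental injection into a vessel. The Background repeats this and adds death as a possible result. Under Study arms, only one of the two groups receives bupivacaine.

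**The concern.** A board that can end or change a randomized trial on safety grounds needs to know whether harm gathers in one arm and, before it acts, which arm that is. Here the protocol has already said which arm it worries about. The blinding rule withholds the fact that would confirm or remove that worry.

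The population makes this more than a formality. Patients have inoperable malignancy and are followed for 4 months or until death, so serious events and deaths unrelated to the injection are to be expected in both groups. Against that background a total count says little about either treatment.

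At stake is the protection of patients still to be enrolled. The article reports 36 recruited; with 90 per group the total is 180, so 180 − 36 = 144 were still to come when it was written.

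**Working it through.** The document gives no figure to reproduce on this point. The check is a reading of the text, followed by an illustration.

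**Step 1: what the board can learn under each format that the text allows.** Being blinded to allocation is compatible with two kinds of report.

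| Closed-session data | Can the board see an imbalance? | Can it tell which treatment carries it? |
|---|---|---|
| Pooled over arms | No | No |
| By coded arm (A/B), code never opened | Yes | No |
| By coded arm, code opened on request | Yes | Yes |

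The first two rows comply with the blinding sentence. The third does not, and it is the only one in which a vote to modify or terminate can rest on knowing which treatment is involved.

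**Step 2: what pooling conceals.** Inputs: 90 per group (Sample size calculations) and 1:1 allocation (Randomization and blinding). The event counts are assumptions, since the article gives no expected rate of serious events.

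For *k* events in 180 patients, the pooled rate is *k*/180 whatever the split. The two-sided Fisher p-value sums the hypergeometric probabilities C(90, a) × C(90, k − a) / C(180, k) over all splits no more likely than the one observed.

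For 6 events:
- Pooled rate = 6/180 = 3.3%.
- Split 3 v 3: p = 1.00.
- Split 6 v 0: p = 2 × C(90, 6)/C(180, 6) = 2 × (90·89·88·87·86·85)/(180·179·178·177·176·175) = 2 × 0.01434 = 0.029.

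For 8 events:
- Pooled rate = 8/180 = 4.4%.
- Split 4 v 4: p = 1.00; 7 v 1: p = 0.064; 8 v 0: p = 0.007.

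At half recruitment (45 per group), 6 events are 6/90 = 6.7% pooled, and a 6 v 0 split has p = 0.026.

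A board given only the total cannot tell these splits apart.

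**Step 3: what a code without a key leaves open.** Suppose the table reads A = 6, B = 0. The p-value is the same whichever letter stands for bupivacaine. The result would either support the hazard that the article names or point at the alcohol-only arm, and those are opposite conclusions. The board would have to vote without knowing which one it faced.

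**The case against.** Much of the case on the other side stands.

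- **Blinded does not mean pooled.** A reader might infer that the board cannot see any excess of harm. The document does not support that. A board shown arms A and B is still blinded to allocation and would see an imbalance, and the article does not say which format is used. The limit certain under either format is on attribution.
- **The closed session has a use without by-arm data.** Discussion in the absence of the principal investigator and the statistician is a purpose in itself, so the session is not empty.
- **The vote is not placed in the closed session.** It comes at the end of each meeting, and the text does not tie it to arm-specific harm alone. The board also hears about compliance, quality control and follow-up.
- **The named harm may show itself.** A cardiac arrest at the moment of injection would stand out as a single case, and vital signs are taken just before and just after neurolysis. Pooling does more to hide later or less specific events.
- **The illustration is only that.** The counts are assumed and chosen to show a contrast. The planned recruitment of a year and a half with three-monthly meetings gives about 18/3 = 6 looks, so a single p near 0.03 would not by itself be grounds for stopping.

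The objection that does not succeed is that this is detail for a charter. Table layouts and review criteria may well be set at the first meeting. The blinding rule, however, is stated in the article separately and without exception, so a charter that allowed unmasking would contradict it. Blinding the board is also not needed to keep the patient and the research nurse blinded. Those are the only two parties whose blinding is described under Randomization and blinding, and board members take no part in running the trial.

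**Conclusion.** The point holds in a limited form. As written, the protocol gives the board a safety vote and denies it, without exception, the knowledge of which arm is which. If data are pooled, an imbalance is invisible. If they are coded, an imbalance is visible but cannot be assigned to the bupivacaine arm, whose specific risk the protocol itself raises.

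The size cannot be stated as a rate, because the document gives no expected frequency of serious events. The figures above show only that one pooled rate is compatible with perfect balance and with marked imbalance (3.3% for both 3 v 3 and 6 v 0).

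The conclusion rests on reading the blinding sentence as covering all sessions and the vote, which is its plain meaning. A charter that is not shown could add to the arrangements, but the sentence would still need changing to agree with it. The point does not affect the primary analysis or any stated figure. It weakens safety monitoring and is easily put right.

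**What to change.** Replace the sentence that blinds each reviewer with text such as:

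*Closed-session safety data will be presented to the DSMB by coded arm (A/B), prepared by a person independent of the trial team, and the DSMB may unmask the code on request. These tables will not be shown to the PI, the trial statistician or the research nurse.*

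The cost is one coded table per three-monthly meeting and an independent person with access to the allocation list. An independent third party already prepares the envelopes from that list, but the article does not say that this party keeps it, so the role needs to be assigned. As a protocol modification the change goes to the research ethics board, as the Trial status section requires.

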## Patient confidentiality

Following the signature of informed consent, participants will be given a unique identifier (ID). This study ID will be used in the main database containing study-related data. No identifying information including name, date of birth, or hospital unit number will be in the main database to protect participant confidentiality. A separate password-protected file will contain participants name and study ID information. Only the PI will have access to this file. All data will be stored for 10 years following the study completion or as requested by the standard operating procedure of the CRCHUM.

## Data Availability

The datasets used and/or analyzed during the current study are available from the corresponding author on reasonable request.
